## Abstract

**Background:**

Musculoskeletal disorders are common and costly disorders to workers compensation and motor accident insurance systems and are a leading contributor to the burden of ill-health. In Australia, vocational rehabilitation is provided to workers to assist them to stay in, or return to work. Self-management training may be an innovative addition to improve health and employment outcomes from vocational rehabilitation.

**Methods/Design:**

The research plan contains mixed methodology consisting of a single blind randomised controlled trial, an economic evaluation and qualitative research. Participants (n = 366) are volunteers with compensated musculoskeletal disorders of 3 months to 3 years in duration who were working at the time of the injury/onset of the chronic disorder. The trial tests the effectiveness of usual vocational rehabilitation plus the Chronic Disease Self-Management Program (CDSMP) to which two additional and newly-developed modules have been added, against vocational rehabilitation alone (control) The modules added to the CDSMP focus on how to navigate through compensation systems and manage the return to work process, and aim to be relevant to those in a vocational rehabilitation setting.

The primary outcome of this study is readiness for return to work which will be evaluated using the Readiness for Return-to-Work scale. Secondary outcomes include return to work status, health efficacy (heiQ™ questionnaire) and general health status (SF-12v2^® ^Health Survey). Measures will be taken at baseline, immediately post-intervention and at 6- and 12- months post-intervention by an independent assessor. An economic evaluation will compare the costs and outcomes between the intervention and control groups in terms of cost-effectiveness and a partial cost-benefit or cost analysis. The impact of the intervention will also be evaluated qualitatively, in terms of its acceptability to stakeholders.

**Discussion:**

This article describes the protocol for a single blind randomised controlled trial with a one year follow-up. The results will provide evidence for the addition or not of self-management training within vocational rehabilitation for chronic compensated musculoskeletal disorders.

**Trial Registration:**

Australia and New Zealand Clinical Trials Registry ACTRN12609000843257

## Background

Arthritis and musculoskeletal conditions are responsible for the third largest proportion of health expenditure and are a national health priority for Australia [1]. They are responsible for over 50% of claims in Australian workers compensation schemes [2]. There is a strong evidence-base for early return to work as a part of the management of these conditions [3]. The International Labour Organisation defines vocational rehabilitation as activities which enable a disabled person to secure and retain suitable employment [4]. This includes medical, psychological, social and occupational activities which aim to re-establish the working capacity of sick or injured persons with a previous work history as well as provide the prerequisites for returning to the labour market [5]. Thus, vocational rehabilitation incorporates work re-training, education and counselling, work guidance, ergonomic modifications and psychosocial strategies.

Vocational rehabilitation has grown significantly in Australia since the 1980s in response to rapidly rising workers' compensation costs and following the introduction of vocational rehabilitation into workers compensation legislation [6]. The rationale underpinning its availability is cost savings for communities and employers and the improved health of individuals through early return to work. However, vocational rehabilitation does not have a substantial evidence-base to support its effectiveness [7], and so has come under question especially with the rising cost of the growing vocational rehabilitation industry [8-10]. In addition, a recent review [11] criticised vocational rehabilitation for coming too much under the influence of economic rationalism and called for a return to its humanitarian core. The review proposed that ideas being put forward in relation to health reform, including self-management, could assist with this aim.

Self-management is an approach used increasingly in chronic illness care to improve self-efficacy and wellness behaviours [12]. It has been defined as the learning and practising of the skills necessary to conduct an active and emotionally satisfying life while living with a chronic condition [13]. Self-management programs aim to help participants make informed choices and then carry them out [13]. Key self-management skills include; problem solving, decision making, resource utilization, forming partnerships with healthcare providers and taking action [14]. Program participants are up-skilled in personalised goal setting and action care planning, and collaborative problem definition is based on their readiness to change and self-efficacy. Chronic disease self-management programs have been shown to improve clinical outcomes and health care utilisation in some chronic diseases [12,15].

This research will investigate the benefit or not of adding self-management to usual vocational rehabilitation for injured persons who have transitioned from the acute to chronic stage of a musculoskeletal condition. The Chronic Disease Self-Management Program (CDSMP), developed at the Stanford University [16], was chosen for use in this research as it was judged to be the most appropriate for the study population. For the purposes of this research, two new modules have been developed and added to the CDSMP to tailor the self-management intervention to those participating in vocational rehabilitation and seeking to return to work post-injury.

Three hypotheses drive this research: first, that a greater proportion of individuals who participate in the self-management program will be classified as ready to return to work based on a validated scale; second, that adding self-management to vocational rehabilitation will result in a more efficient use of resources and third, that the self-management intervention will be acceptable to vocational rehabilitation clients, health care providers, policy makers and regulators.

The aims of this research are:

1. To develop an intervention to add self-management to vocational rehabilitation for individuals with chronic compensated musculoskeletal disorders.

2. To test the effectiveness of self-management plus usual vocational rehabilitation against usual vocational rehabilitation alone.

3. To undertake an economic evaluation of adding self-management to usual vocational rehabilitation practice.

4. To determine the acceptability of the intervention to clients, their vocational rehabilitation providers, policy makers and regulators.

## Methods/Design

The methodology below was developed by the scientific research team in consultation with the industry partners.

### Design

The design is mixed methods research consisting of a single blind randomised controlled trial, an economic evaluation and qualitative research. The trial will test an intervention of self- management training plus usual vocational rehabilitation against usual vocational rehabilitation care only. Ethical approval has been granted from the Human Research Ethics Committee of The University of Queensland (2009000579). Informed written consent will be obtained from all participants.

### Participants

Participants will comprise eligible volunteers who are clients either referred to a national provider of occupational health services and vocational rehabilitation or referred directly to the trial by their insurer. Recruitment will be undertaken in two Australian cities. To be eligible for the study volunteers will have: a diagnosed, compensated musculoskeletal disorder of 3 months or more but not longer than 3 years in duration; been working at the time of the injury/onset of the chronic disorder; and English language and literacy skills that are adequate to complete the study requirements including participating in the self-management course. In addition, there must be written agreement by the payer (insurer) for the individual to participate. Individuals will not be eligible if they have signs and symptoms suggestive of non musculoskeletal conditions (e.g. tumour, systemic illness, inflammatory disease or infection), their primary condition is a psychological/psychiatric or neurological disorder, or if they have previously participated in a vocational rehabilitation, chronic pain, functional restoration or work hardening program as these may contain a self-management component.

The sample size calculation was based on the primary outcome readiness for return to work status at 12 months post-intervention. A power calculation was performed assuming that the proportion ready to return to work in the usual care group would be 30% and the proportion in the self-management group would be 45%. Accounting for a 10% loss to follow-up, a total of 183 participants were required in each study arm (total n = 366) for the study to achieve 80% power.

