### Intervention

The control group will receive usual vocational rehabilitation only. The intervention group will receive vocational rehabilitation plus the self-management intervention which has been termed Self-Management for Return to Work (SMRTW). It comprises eight, two-hour weekly sessions specifically, the six modules of the CDSMP plus two new modules relevant to a vocational rehabilitation setting. The SMRTW program will be conducted for groups of 8-10 participants. The new modules were developed to compliment the format and approach of the CDSMP. In order to be classified as having received the intervention, participants must attend at least five of the eight sessions including at least one of the new module sessions.

In developing the two additional modules, the research team consulted industry partners including a national leader in occupational and vocational rehabilitation and experts in self-management training. The (new) module titled *Navigating the System *aims to: assist the client understand the agency funding their rehabilitation, its function and services; encourage them to use problem-solving skills to deal with 'system' issues; and, enhance their knowledge of the various persons in the 'system' and their respective roles. The (new) module titled *Managing Return-to-Work *aims to assist the client to understand: their role in the return to work process; the factors enhancing and limiting the success of return to work; and, the implications of having people with injuries in the workplace for employers and co-workers. As this is the final module delivered in the program, participants are also encouraged to reflect on the skills they have learnt during the program and to plan for their futures.

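### The exclusion meant to keep out people with earlier self-management exposure does not name self-management courses, so as written it admits graduates of the CDSMP itself

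*Protocol article*

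**What the plan says.** The protocol article's Participants section bars volunteers who have "previously participated in a vocational rehabilitation, chronic pain, functional restoration or work hardening program as these may contain a self-management component". Four programme types are named, and the closing clause gives the reason for naming them.

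The Intervention section describes the experimental programme, Self-Management for Return to Work (SMRTW), as eight weekly sessions: "the six modules of the CDSMP plus two new modules relevant to a vocational rehabilitation setting". The Design section gives the comparison as "self- management training plus usual vocational rehabilitation against usual vocational rehabilitation care only".

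The Background remarks that "Self-management is an approach used increasingly in chronic illness care to improve self-efficacy and wellness behaviours". The items listed under Baseline data do not include earlier self-management training.

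For sample size, the Participants section assumes 30% ready to return to work under usual care and 45% with self-management at 12 months. It allows 10% loss to follow-up and arrives at 183 per arm "for the study to achieve 80% power".

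**The concern.** The rule and its reason do not match. The four named programme types are excluded because they might include some self-management. A course that consists of self-management is not named. The list is also closed: it has no wording such as *or similar*, whereas the exclusion of non-musculoskeletal conditions in the same sentence is introduced with examples. Someone who completed the CDSMP on its own and attended none of the four listed programmes therefore meets the criteria, although that person has already had the content of six of the eight trial sessions.

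What is at stake is the size of the contrast. A graduate allocated to control has already had part of the test treatment. A graduate allocated to SMRTW has less left to gain. Both pull the observed difference towards zero, in readiness for return to work and in the heiQ domains, which the protocol uses to capture the more immediate effects of self-management courses. Planned power is close to 80%, so there is little slack.

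**Working it through.** **Does anything else in the article close the gap?**

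- The other criteria under Participants cover disorder type and duration, work status at onset, language, payer agreement, and other primary conditions. None concerns earlier courses.
- The eligibility decisions in the Discussion deal with psychiatric co-morbidity, duration of the condition and type of compensation. They do not mention it.
- The items under Baseline data do not record it, so on what is listed it could be neither adjusted for nor examined in a sensitivity analysis.
- The mid-study audit of 40 case files (Qualitative analysis) looks at whether the provider's usual care is changing. It is not designed to find courses taken elsewhere before enrolment.
- Self-management delivered inside one of the four listed programmes is already excluded. The gap concerns stand-alone courses only.

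**The plan's own figure.** Inputs from Participants: p_C = 0.30, p_I = 0.45, power 80%, loss 10%. The significance level is not stated; two-sided 5% is assumed.

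n = [1.960·√(2·p̄·(1−p̄)) + 0.842·√(p_C(1−p_C) + p_I(1−p_I))]² / (p_I − p_C)², with p̄ = 0.375.

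= [1.960·√0.46875 + 0.842·√0.4575]² / 0.0225 = 162.3, so 163 per arm.

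163 / 0.9 = 181.1, so 182 per arm against the stated 183. The figure reproduces. A one-sided 5% test would give 128, inflated to 143, so the two-sided assumption fits the plan.

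**Planned power.** Evaluable per arm: 183 × 0.9 = 164.7.

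Power = Φ{[(p_I − p_C)·√n − 1.960·√(2·p̄·(1−p̄))] / √(p_C(1−p_C) + p_I(1−p_I))} = Φ(0.862) = 80.6%.

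**Dilution.** Let f be the share of recruits who are graduates, equal in both arms by randomisation. In the worst case they gain nothing further, and the difference becomes 15·(1 − f) points. Two positions for graduates are tried:

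- A: they sit at 45% in both arms, so p_C = 0.30 + 0.15f and p_I = 0.45.
- B: they sit at 30% in both arms, so p_C = 0.30 and p_I = 0.45 − 0.15f.

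| f (assumed) | Difference, points | Power, A | Power, B | Per arm for 80% power, with 10% loss |
|---|---|---|---|---|
| 0 | 15.0 | 80.6% | 80.6% | 182 |
| 2% | 14.7 | 78.9% | 79.0% | 188-189 |
| 5% | 14.25 | 76.2% | 76.6% | 200-202 |
| 10% | 13.5 | 71.4% | 72.1% | 223-226 |

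Where graduates sit hardly matters; the share f drives the result.

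**Partial gain.** If graduates keep half the benefit, the difference is 15·(1 − f/2). A 10% share then gives 14.25 points, the same as the 5% row: about 76-77% power.

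**The case against.** The case for leaving the criterion alone has several parts.

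*Exposure may be rare.* No share of earlier graduates is documented. A reader might infer from the Discussion that co-morbidity is common and hence that many recruits have attended chronic-disease courses. The text does not support that: the remark singles out psychiatric conditions and says nothing about courses. The Background sentence on increasing use is general, and the Abstract presents self-management as an innovative addition in this setting. This stands. The article supports the possibility of such recruits, not a number.

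*Graduates in control are not fully treated.* A reader might infer that they have already received the intervention. They have not. SMRTW is the CDSMP plus two modules on the compensation system and return to work. The Discussion says the generic programme was judged suitable with those modules added, and the Intervention section requires at least one new-module session before someone counts as having received the programme. The primary outcome is readiness for return to work, the subject of one of those modules. This also stands: zero further gain is an upper limit on the loss.

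*There is no bias.* Randomisation balances graduates between arms, so nothing here favours either group. For the continuous outcomes, baseline scores enter the model as covariates, which handles differing starting levels but does not restore a lost contrast. This stands as well.

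*The article is condensed.* Screening questions may sit in the full protocol. That is possible, and if such courses are named there the point falls away. But the article is not silent on the criterion: it states both the list and its purpose, and the two do not fit. That is a fault in what is written, not an omitted detail.

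**Conclusion.** The point holds as a mismatch between an exclusion and its own stated purpose: graduates of stand-alone self-management courses, including the CDSMP, are eligible as the criterion is written. That conclusion rests on the wording alone and needs none of the arithmetic.

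The size is unknown and may well be small. The power figures in the table rest on an assumed exposed share, an assumed two-sided 5% level, no further gain for graduates, and the 30% and 45% rates applying to people without earlier training. At a 2% share the worst-case loss is under two percentage points of power; at 10% it is roughly nine. Any benefit from the two new modules reduces these losses.

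A reader might go further and conclude that the trial is biased, or that 183 per arm is miscalculated or inadequate. The documents support none of this. The effect is dilution towards zero, the sample size reproduces, and without a figure for earlier attendance there is no basis for calling the trial underpowered. The change is worth making because it is cheap and the protocol already treats earlier exposure as a reason to exclude.

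**What to change.** In the Participants section, extend the prior-programme exclusion with *or a structured self-management course, including the CDSMP*, and ask about such courses at screening.

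The cost is one clause, one screening question and the loss of a few volunteers. The target of 183 per arm does not change.

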### Randomisation

Volunteers accepted into the study will be randomised into an intervention or control group by an independent body using a randomised permuted block design. Prior to randomisation, participants will be stratified by state to cater for local regulations and conditions. The scientific research team are blinded to the randomisation process and all data collection.

### Intervention

The control group will receive usual vocational rehabilitation only. The intervention group will receive vocational rehabilitation plus the self-management intervention which has been termed Self-Management for Return to Work (SMRTW). It comprises eight, two-hour weekly sessions specifically, the six modules of the CDSMP plus two new modules relevant to a vocational rehabilitation setting. The SMRTW program will be conducted for groups of 8-10 participants. The new modules were developed to compliment the format and approach of the CDSMP. In order to be classified as having received the intervention, participants must attend at least five of the eight sessions including at least one of the new module sessions.

In developing the two additional modules, the research team consulted industry partners including a national leader in occupational and vocational rehabilitation and experts in self-management training. The (new) module titled *Navigating the System *aims to: assist the client understand the agency funding their rehabilitation, its function and services; encourage them to use problem-solving skills to deal with 'system' issues; and, enhance their knowledge of the various persons in the 'system' and their respective roles. The (new) module titled *Managing Return-to-Work *aims to assist the client to understand: their role in the return to work process; the factors enhancing and limiting the success of return to work; and, the implications of having people with injuries in the workplace for employers and co-workers. As this is the final module delivered in the program, participants are also encouraged to reflect on the skills they have learnt during the program and to plan for their futures.

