### Procedures

#### Preparation of Facilitators

The SMRTW program will be facilitated by two people: a lay facilitator trained in the self-management model and a vocational rehabilitation practitioner. The practitioners (n = 5) are employees of one of the project's industry partners, a national provider of vocational rehabilitation services. They will undertake an accredited four day train-the-trainer training program in self-management conducted by Arthritis Queensland.

A flow chart of the trial is presented in Figure 1. The recruitment period will be 18 months. Participants will be notified by the project manager via telephone when sufficient participants are recruited to constitute an intervention, and control group. This notification will occur up to two weeks prior to the commencement of an eight-week intervention period. The self-management sessions will be conducted at the offices of the vocational rehabilitation provider involved in the research. Outcome data will be collected via a telephone interview. In addition, to assess the uptake of the intervention, recruiting organisations will be asked to record the number of non-volunteers and their reasons for not participating.

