### Data Analysis

Analysis of the effectiveness of the SMRTW program will be performed on an intention to treat basis and per protocol. Primary outcomes of interest are those collected at 12 months post-intervention. The differences in the mean scores of the continuous variables will be analyzed using multivariate regression and the difference in the proportion of the dichotomous outcomes (e.g. the proportion 'ready to return to work') will be analyzed using logistic regression.

Continuous outcome measures will be analyzed using multi-level modeling to describe within participant differences over time and to account for the repeated measures design component of the study. In the modeling of continuous outcomes, the baseline measures collected pre-intervention will be included as covariates in the model. Based on the results observed, participant, time and intervention will be defined as fixed or random effects as appropriate. Similarly, multivariate logistic regression will be used to assess dichotomous (1/0) outcomes. The effect of the SMRTW program on the outcomes at the earlier time points (i.e. immediately and 6 months post-intervention) will also be analyzed after appropriate adjustments to the significance level to account for multiple testing.

In regards to the economic evaluations, service utilisation, cost and work outcome data will be obtained from the questionnaires administered to participants at the four data collection time points. Estimates of these measures for the intervening time periods shall be determined by linear interpolation. Summary data on the measures will be presented and compared statistically for the two groups.

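### The self-management programme is delivered in groups of 8-10 in one arm only, but neither the sample size nor any named model allows for clustering by treatment group

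*Protocol article*

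**What the plan says.** The Randomisation section allocates individuals in permuted blocks, stratified by state. Under Intervention, the control arm has usual vocational rehabilitation alone, and the other arm adds eight weekly two-hour sessions: "The SMRTW program will be conducted for groups of 8-10 participants". Under Preparation of Facilitators, the programme is run by a lay facilitator together with a vocational rehabilitation practitioner: "The practitioners (n = 5) are employees of one of the project's industry partners".

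The sizing is in the Participants section: "The sample size calculation was based on the primary outcome readiness for return to work status at 12 months post-intervention". It takes 30% ready to return to work under usual care and 45% with self-management. The only inflation given is for attrition: "Accounting for a 10% loss to follow-up". The result is that "a total of 183 participants were required in each study arm (total n = 366) for the study to achieve 80% power".

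Data Analysis assigns logistic regression to dichotomous outcomes, which include the primary one. For the others: "Continuous outcome measures will be analyzed using multi-level modeling to describe within participant differences over time". The effects listed for that model are participant, time and intervention. Treatment group and facilitator are not mentioned.

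**The concern.** People who sit through an eight-week course together, with the same two facilitators and the same peers, may end up with more similar outcomes than people drawn at random from the arm. With 183 in the intervention arm there would be about 183/10 = 18 to 183/8 = 23 such groups. Controls have no comparable group programme. This is an individually randomised trial with possible clustering in one arm.

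The multi-level model deals with a different dependence: repeated measurements on one person. It does not deal with several people sharing a group.

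If within-group correlation exists and is ignored, the confidence interval for the primary effect is too narrow and the false-positive rate exceeds its nominal level, in the direction that favours a positive finding. If it is modelled properly, the planned numbers give less than the stated power. The trial is meant to inform whether self-management training is added to vocational rehabilitation, so the precision of the primary comparison matters.

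**Working it through.** **Inputs from the article.** Proportions 0.30 and 0.45; 10% loss; 183 per arm; 80% power; intervention groups of 8-10.

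**Assumed, because not stated.** Two-sided 5% test (the one-sided variants give 143 or 157 per arm and do not match 183); ICC from 0.01 to 0.10; equal group sizes; clustering in the intervention arm only.

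**Step 1: reproduce the stated figure.** With mean proportion 0.375 and pooled variance under the null:

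n = [1.960 × √(2 × 0.375 × 0.625) + 0.842 × √(0.30 × 0.70 + 0.45 × 0.55)]² / 0.15²
= [1.960 × 0.6847 + 0.842 × 0.6764]² / 0.0225, about 162.3, so 163 per arm.

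163/0.9 = 181.1, so 182 against the stated 183. No design effect is needed to reach it.

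**Step 2: slack at ICC 0.** Analysed per arm: 183 × 0.9 = 164.7.

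SE under the null = √(0.234375 × 2/164.7) = 0.05335. SE under the alternative = √(0.4575/164.7) = 0.05270.

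Power = Φ[(0.15 − 1.960 × 0.05335)/0.05270] = Φ(0.862) = 80.6%.

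**Step 3: clustering in the intervention arm.** Design effect D = 1 + (m − 1) × ICC, applied to that arm's variance only:

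- SE under the null = √[0.234375 × (1 + D)/164.7]
- SE under the alternative = √[(0.21 + 0.2475 × D)/164.7]
- Ratio of true to naive SE = √[(1 + D)/2]
- True error of a nominal 5% test that ignores groups = 2 × [1 − Φ(1.960/ratio)]

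Example, m = 8 and ICC 0.05: D = 1.35; the SEs are 0.05783 and 0.05748; power = Φ[(0.15 − 0.11334)/0.05748] = Φ(0.638) = 73.8%. The ratio is √1.175 = 1.084 and the true error is 7.1%.

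The ranges below run from m = 7.2 (a group of 8 after 10% loss) to m = 10 (no loss within the group).

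| ICC (assumed) | Power if groups are modelled | SE ratio | True error if groups are ignored |
|---|---|---|---|
| 0 | 80.6% | 1.00 | 5.0% |
| 0.01 | 79.3% to 78.8% | 1.015 to 1.022 | 5.4% to 5.5% |
| 0.02 | 78.1% to 77.0% | 1.031 to 1.044 | 5.7% to 6.0% |
| 0.05 | 74.6% to 72.0% | 1.075 to 1.107 | 6.8% to 7.7% |
| 0.10 | 69.1% to 64.6% | 1.145 to 1.204 | 8.7% to 10.4% |

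The power and error columns are alternatives, according to how the data are analysed; they do not add together.

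**Step 4: thresholds.** Power falls below 80% once the ICC exceeds about 0.0041 (m = 8), 0.0036 (m = 9) or 0.0032 (m = 10). For scale, keeping 80% power with m = 8 to 10 would take 376-378 participants in total at ICC 0.01, 388-396 at 0.02, 428-446 at 0.05 and 492-530 at 0.10.

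Clustering by practitioner (five, so about 164.7/5 = 33 analysed participants each) is left out of all these figures.

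**The case against.** A reader might infer that the trial fails to deliver 80% power and that its standard errors are too small. The article does not support that as a statement of fact. It gives no ICC, and group delivery makes correlation plausible without establishing it. At ICC 0.01 the power loss is one to two points and the SE is understated by about 2%. The outcome is an individual's readiness 12 months after a short course, and the intention-to-treat set includes people who attended few sessions; both could weaken within-group correlation. This part of the objection stands, and it is why the point is conditional.

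Second, the article is condensed, and a full protocol or SAP could add a group term. This stands in part. The article does not say that every model treats participants as independent, and it leaves the choice of fixed or random effects open. But it does list the effects concerned, and treatment group is not among them. Nor can a later plan make the published power statement allow for clustering, because that calculation is complete and reproduces without it.

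Third, the Procedures section suggests that intervention and control groups are assembled together. Correlation from shared calendar time or city would then touch both arms and largely cancel in the comparison. That is fair: only correlation arising from the sessions and facilitators inflates the variance. This is the component that the assumed ICC is meant to represent, and the reason the design effect is applied to one arm. Applying it to both would exaggerate the loss.

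**Conclusion.** The omission is clear: the sample size allows only for loss to follow-up, and no named model includes the treatment group. The consequence depends on the ICC. It is minor at 0.01, worth reporting at 0.02 (power 77-78%), and substantial at 0.05 (72-75%) and 0.10 (65-69%). Because the sizing starts at 80.6%, 80% power is available only if the ICC is essentially zero. These figures rest on a two-sided 5% test, 10% loss, roughly equal groups and clustering in one arm; the ICC values are assumptions. This should be fixed, chiefly to protect the primary confidence interval and p-value, but the article does not show that the trial's conclusions would be invalid.

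**What to change.** 1. Record the treatment group and facilitators for every intervention participant as randomised, including non-attenders who were assigned to a group. Attendance has to be tracked anyway for the rule defining who received the intervention, so this should need little more than one extra variable. It should be captured during delivery, since it may not be recoverable later.
2. Analyse the primary outcome with a partially nested logistic model: a random effect for treatment group in the intervention arm only, with controls as singletons. Do the same in the continuous models, alongside the existing within-participant level. Cluster-robust errors with a small-sample correction, again with controls as singletons, are an acceptable alternative; the correction matters with only about 18-23 groups.
3. In the sample-size paragraph, state that 183 per arm gives 80% power only if the ICC is essentially zero, and show power over an assumed ICC range such as the one tabulated above.

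The cost is wording, one recorded variable, slightly wider intervals and a less favourable stated power. No extra participants are needed. The change corrects the analysis and the power statement; it does not restore 80% power if the ICC is material, and the report should say so.
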